### Secondary objectives

To investigate associated changes between: child symptoms, on the one hand, and 1) child responses (i.e., child emotional, behavioral, and cognitive responses), 2) parental availability and 3) parent-child interaction on the other, we will use the stepwise procedure in multivariate regression analyses with a maximum of 4 tested predictors. With a sample size of 100, alpha of .05 and medium effect size (f^2^ = .15), we will achieve a power of .87 in analyses with 4 individual predictors. We will use latent variables for child responses, parental availability and parent-child interaction.

We will also use multivariate regression analyses to study the fourth goal, namely which mechanisms explain how the two components added to the TF-CBT-based Horizon treatment contribute to the effectiveness of TF-CBT-based Horizon treatment. We will follow Holmbeck’s recommendations [120] for these mediational analyses and will test the robustness of our results by using the bootstrapping method. These analyses will allow us to determine whether the parent-child interaction variables and parental availability partly or fully mediate the effects of each parental component on child symptoms. Specifically, we will test whether, as predicted, the preparatory program leads to increased parental availability and whether the parent-child interaction sessions lead to improved parenting behavior. Also, we will explore whether these changes lead to a reduction in symptoms. Because at least partial mediation is assumed, a small to medium effect size is chosen (f^2^ = .10). Two models are tested. A first model with component 1 (preparatory parent program) and parent availability as independent variables. And a second model with component 2 (parent-child interaction sessions) and parent-child interaction as independent variables. With a sample size of 100, alpha of .05 and medium effect size (f^2^ = .10), we will achieve a power of .80 if 2 predictors are tested in the regression.

*Exploratory analyses: Cross-lagged panel model.* Based on the recommendations of Kazdin [47] to investigate mediators and mechanisms of change in intervention RCT’s, to test the causal direction of the longitudinal relation between the different types of mediators and child outcomes, we will conduct cross-lagged panel analyses [121]. The model will include three waves of child symptoms and parent-child variables, parental availability, and child responses, respectively. We will estimate T1 associations (interpreted as correlations at T1), T2 and T3 stability (interpreted as relative stability over time), correlated change (interpreted as overlapping relative change in two variables), and cross-lagged paths between child symptoms and parent-child variables, parental availability, and child responses, respectively (interpreted as a linkage of the level of one variable at a given time point with a relative change in another variable one assessment later). Correlated change and cross-lagged paths reflect longitudinal relationships, and will be interpreted as such. These cross-lagged analyses will also be carried out with the repeated measures at session 1, 9 and 15 for child trauma symptoms, closeness and time spent together with possibilities to explore more than three waves of measurements.

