### Secondary objectives

Our second goal is to evaluate the effects of these two parental treatment components on child adjustment. Our third goal is to investigate mechanisms underlying the efficacy of treatment for children who have been exposed to IPV by examining associations between: child symptoms, on the one hand, and, 1) child responses (i.e., child emotional, behavioral, and cognitive responses, 2) parental availability and 3) parent-child interaction, on the other.

Our fourth goal is to examine specific hypotheses of change. Specifically, we will test whether, as predicted, the preparatory program leads to increased parental availability and whether the parent-child interaction sessions lead to improved parenting behavior. Also, we will explore whether these changes lead to a reduction in symptoms.

To ensure comparability of the randomized conditions, we will control for duration and severity of the IPV [45], parental psychopathology [46], and new incidents of IPV.

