### Statistical analyses and sample size calculation

All variables are measured on at least an ordinal scale. All scale scores will be examined for normality. Should we observe deviations, steps will be taken to ensure optimal estimation of parameters in our analyses. The proposed study includes a nested structure, because individuals are treated within groups. Following the recommendations by Peugh [118], we will calculate design effects to assess group-level dependency and examine whether multi-level modeling is required. To ensure comparability of the randomized conditions, we will control for duration and severity of the IPV [45], parental psychopathology [46], and new incidents of IPV. Power calculations were performed using the program G*power 3 [119], assuming that individual-level effects can be treated as independent data. We determine required sample size to be 100 parent-child dyads, achieving statistical power of at least .80 for the primary and secondary objectives, as described in more detail in the following paragraphs. We will test for the randomness of missing data. If this is the case we will use multiple imputation.

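### The association analyses of the third goal use stepwise selection, but the .87 power quoted for them belongs to the overall F test of four predictors entered together

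*Protocol article*

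**What the plan says.** In the Secondary objectives part of the statistical section, the protocol article turns to the associations between child symptoms and three domains: child responses, parental availability and parent-child interaction. For these, "we will use the stepwise procedure in multivariate regression analyses with a maximum of 4 tested predictors". At N = 100, alpha .05 and f2 = .15, "we will achieve a power of .87 in analyses with 4 individual predictors". The domains are to be represented as latent variables: "We will use latent variables for child responses, parental availability and parent-child interaction".

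Three other statements bear on this.

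- The objectives section gives the purpose: "Our third goal is to investigate mechanisms underlying the efficacy of treatment for children who have been exposed to IPV by examining associations between" symptoms and the three domains.
- The opening of the sample size section says how power was obtained, "Power calculations were performed using the program G*power 3 [119], assuming that individual-level effects can be treated as independent data", and claims adequacy for these analyses too: "We determine required sample size to be 100 parent-child dyads, achieving statistical power of at least .80 for the primary and secondary objectives".
- A robustness check appears only for the mediation models of the fourth goal, where the authors "will follow Holmbeck’s recommendations [120] for these mediational analyses and will test the robustness of our results by using the bootstrapping method".

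The article gives no entry or removal criterion and no candidate list for the stepwise analyses. Only the cross-lagged models are labelled exploratory.

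**The concern.** On its ordinary reading, a stepwise procedure lets the data choose which predictors stay and then fits the chosen model to the same data. The usual p-values and intervals assume that the model was fixed beforehand, so after selection they no longer have their nominal error rate or coverage. The power quoted is that of a fixed-model test with a 5% error rate, so method and power figure describe two different analyses.

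At stake is what the trial can say about which parental and child processes go with symptom change. The article's own theory links the domains, so correlated predictors are the realistic case. When a correlated predictor is dropped, the one kept takes over part of its association. A paper could then report one process as strongly associated and another as not, largely because of the selection. With at most four theory-based predictors and 100 dyads, there is little need to select.

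**Working it through.** **Inputs from the article.** N = 100, alpha = .05, f2 = .15, four predictors, independent observations, stated power .87.

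**1. Reproducing the stated power.** For the overall F test of a fixed regression with u predictors, v = N - u - 1 and lambda = f2 x N.

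- u = 4: v = 100 - 4 - 1 = 95, lambda = .15 x 100 = 15. Power from the noncentral F = .8735 (stated .87).
- The article's other two powers reproduce by the same formula: u = 5, f2 = .15 gives .8430 (stated .84); u = 2, f2 = .10 gives .8026 (stated .80).

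The .87 is therefore arithmetically right, and it is the power to reject the hypothesis that all four coefficients are zero, with all four in the model.

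**2. Assumptions for the stepwise procedure, since the article gives none.** Forward entry at p<.05, removal at p>.10, four candidates, N = 100, normal errors, no clustering, observed rather than latent predictors, pairwise correlation 0, .3 or .5. At least 2,000 simulated trials per setting.

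**3. No predictor associated with the outcome.** With four independent candidates the chance that at least one enters is about 1 - .95^4 = .185. Simulation gives about .14 to .18 across the three correlations, and every model with an entry also has a final F below .05. The fixed four-predictor F test rejects in about 4 to 5%. If more than four candidates are offered, the figure rises: about 25 to 35% with eight.

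**4. Four equal effects with total f2 = .15.**

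| Correlation | 0 | .3 | .5 |
|---|---|---|---|
| At least one predictor enters | .91 | .97 | .98 |
| Mean number kept, of 4 | 1.8 | 1.5 | 1.2 |
| Kept coefficient / full-model value | 1.5 | 2.1 | 2.7 |
| Coverage of nominal 95% interval, kept coefficients | 93% | 74% | 46% |
| Coverage, all four entered and reported | 95% | 95% | 95% |

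The ratios are pooled over kept coefficients; averaged within each trial first, they are about 2.2 at .3 and 2.8 at .5. The coverage figures for kept coefficients are averaged within each trial first. Pooled over kept coefficients, a repeat of the simulation gives about 78% at .3 and 53% at .5, so the conclusion is the same.

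Most of the inflation with correlated predictors can be seen without simulation. If one of four equal predictors is kept alone, its expected slope is b(1 + 3 x rho): 1.9b at .3 and 2.5b at .5. Selecting on significance adds the rest.

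**5. What comes from stepwise and what does not.** As a comparator, all four predictors were entered together and each coefficient was read at p<.05.

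| Correlation | 0 | .3 | .5 |
|---|---|---|---|
| At least one null coefficient significant | .18 | .17 | .16 |
| Mean number of true predictors significant | 1.87 | .94 | .62 |
| Significant coefficient / true value | 1.45 | 2.02 | 2.53 |

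These are close to the stepwise figures or, for the number detected, lower when predictors are correlated. What joint entry does recover is the 5% error rate of the overall test, and 95% coverage when every coefficient is reported.

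**6. Power for one coefficient under joint entry.** Four equal, uncorrelated effects share f2 as .15 / 4 = .0375 each, so lambda = 3.75 with 1 and 95 degrees of freedom, and power is .48 (simulated .46). Simulated power falls to .24 at correlation .3 and .15 at .5.

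**The case against.** The strongest reply is that the simulated figures mostly reflect N = 100 and the reading of significant coefficients only, not stepwise selection. Step 5 shows that much of this stands. The small number of predictors detected, and part of the coefficient inflation, cannot be charged to stepwise alone, and joint entry will not find more individual predictors. The loss of the overall 5% error rate and the poor coverage under correlation do remain, and joint entry with full reporting removes both.

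A second reply is that the word may mean ordered entry of blocks. The article names the domains in sequence, caps the predictors at four and states no thresholds. If so, the selection objection falls. But the text does not say so, and automated selection is the usual meaning of the term.

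A third is that the kept coefficient validly estimates a different quantity, the association without adjustment for the dropped domains. But which domains are dropped would then vary with the data, so the quantity estimated is not fixed in advance.

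A reader might also infer that .87 is a miscalculation, or that stepwise has less power. Neither is supported: the figure reproduces, and the chance that something enters is above .87 (.91 to .98 here), bought with the inflated error rate. Nor does the article promise a ranking of mechanisms. It speaks of associations, and it addresses mediation separately with named models and bootstrapping.

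**Conclusion.** The point holds in a limited form. The article fixes a stepwise procedure for a secondary analysis that it counts as adequately powered, and it supports this with a power that belongs to another test. Nothing in the document offsets the selection, because the bootstrap is tied to the mediation models.

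Under the assumptions in step 2, the false-positive rate for a significant model is about three times the nominal 5%. With correlations of .3 to .5, intervals for kept coefficients fall well short of 95% coverage of the full-model values. With uncorrelated predictors the coverage loss is small (93%), so that part depends on the correlation, which the article does not give. The thresholds, the number of candidates, equal effects and the use of observed predictors are likewise assumptions.

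The consequence is confined to the third goal. A reader should not carry it over to the primary efficacy regression, which has fixed predictors and is unaffected. The change is advisable rather than essential to the trial.

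**What to change.** In the statistical section on secondary objectives:

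- Replace the stepwise procedure with simultaneous entry of at most four latent predictors, named in advance.
- Test the overall F at .05, and report every coefficient with its confidence interval whether or not it is significant.
- State that .87 is the power of that overall F test under independence. State also that power for a single coefficient is lower: about .46 to .48 with four equal uncorrelated effects, and less if they are correlated.
- If fixed-order block entry was intended, name the blocks and their order instead.

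The cost is a few sentences of text. No data collection, sample size or primary analysis changes.

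### The protocol says the mediation analyses will settle partial versus full mediation, but 100 children cannot support a conclusion of full mediation and the quoted power of .80 is for a different test

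*Protocol article*

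**What the plan says.** The point lies in the Protocol article, in the Secondary objectives paragraph of the statistical section.

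- **Claim.** The analyses are to determine "whether the parent-child interaction variables and parental availability partly or fully mediate the effects of each parental component on child symptoms".
- **Models.** There are two regressions, each with one component and its mediator. The first is described as "A first model with component 1 (preparatory parent program) and parent availability as independent variables"; the second pairs the parent-child interaction sessions with parent-child interaction.
- **Method.** The article follows cited "recommendations [120] for these mediational analyses and will test the robustness of our results by using the bootstrapping method".
- **Power.** The effect size is justified by "Because at least partial mediation is assumed, a small to medium effect size is chosen", and the result is that "we will achieve a power of .80 if 2 predictors are tested in the regression", at N = 100, alpha .05 and f² = .10.

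The paragraph gives no margin for the direct effect, no smallest direct effect of interest and no written rule for calling mediation full.

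**The concern.** Partial mediation needs evidence that an indirect path exists. Full mediation needs more: evidence that nothing of the component's effect is left outside the mediator. That is a claim of absence, and an analysis can support it only by bounding the remaining effect. The article promises the determination without a bound, and the only power figure beside it does not concern the direct effect.

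If the promise is carried into the report, a component that works partly outside parental availability or parent-child interaction could be described as wholly explained by it. Mechanism of change is a stated goal of the trial and features in its Discussion, so such a statement would be read as a finding.

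**Working it through.** **Inputs from the article.** N = 100, alpha .05, f² = .10, two predictors (component and mediator), a 2 × 2 factorial design, and power computed as if children were independent.

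**Assumed inputs, not in the article.** A 50 to 50 split for each component; a component-to-mediator effect a of 0.5 or 0.8 SD; a mediator-to-outcome slope of .3; residual SD of 1 for mediator and outcome; true direct effects d of 0.25 and 0.5. The SD unit below is the residual SD of the outcome.

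**Step 1: reproduce the stated power.** For the omnibus F test of two predictors, λ = f² × N = .10 × 100 = 10, with 2 and 97 degrees of freedom. Power is .803, against .80 stated. The same formula gives .843 for five predictors at f² = .15 (stated .84) and .874 for four (stated .87). The .80 is therefore the power to detect that component and mediator jointly explain variance.

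**Step 2: precision of the direct effect.** Half-width = t(.975, 97) × √[(1/50 + 1/50) / (1 − r²)], where r is the component-mediator correlation and t = 1.985.

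- r = 0: 1.985 × √.04 = 0.397.
- a = 0.5: r = 0.25/√(1 + 0.0625) = 0.243, half-width 0.397/√(1 − 0.059) = 0.409.
- a = 0.8: r = 0.40/√(1 + 0.16) = 0.371, half-width 0.397/√(1 − 0.138) = 0.428.

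The half-width is thus about 0.40 to 0.43 SD. An estimate of exactly zero would still leave direct effects of about 0.4 SD in either direction inside the interval.

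**Step 3: if the criterion were a non-significant direct effect.** The test has noncentrality d × √[25(1 − r²)] on 97 degrees of freedom.

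| True direct effect | Miss rate, a = 0.5 | Miss rate, a = 0.8 |
|---|---|---|
| 0.5 SD | 33% (formula 32.9%, simulation 33%) | 37–38% (formula 36.8%, simulation 37.5%) |
| 0.25 SD | 78% (formula 77.5%, simulation 78%) | 79% (formula 79.0%, simulation 79%) |

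**Step 4: sensitivity.**

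- *Clustering.* Therapy groups of about eight families are randomised whole. With a design effect of 1 + 7 × ICC and assumed ICCs of .05 to .15, the design effect is 1.35 to 2.05. At r = 0 the miss rates become 43 to 59% (0.5 SD) and 81 to 86% (0.25 SD).
- *Scale.* If SD means the total outcome SD and the mediator explains 25% of the variance, then at r = 0 the miss rates fall to about 19% and 70%, and the half-width to 0.397 × √.75 = 0.34.
- *The article's own f².* If all of f² = .10 were the component's unique effect, d = 2√.10 = 0.63 and the miss rate is 12%. If half of it were, d = 2√.05 = 0.45 and the miss rate is 40%. If a quarter, d = 2√.025 = 0.32 and it is 65%.

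**The case against.** **The criterion is not written.** A reader might infer that a non-significant direct effect is the only planned basis for declaring full mediation. The article does not say so. It refers to outside recommendations and adds a bootstrap, and a condensed article may leave the operational rule to a fuller plan. This objection stands, so the miss rates in step 3 are conditional on that rule. It does not remove the point: the article states what the analyses will establish, and the interval width in step 2 holds whatever rule is used.

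**The effect sizes are assumed.** This also stands. Direct effects of 0.25 to 0.5 SD and the path sizes appear nowhere in the article. The most favourable reading of its own f² gives a 12% miss rate, but that reading credits the whole planned effect to the direct path and leaves none for the mediator, which sits badly with the premise that at least partial mediation exists.

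**Smaller trials.** A reader might also infer that the smaller the trial, the more often full mediation would be declared. That is true only among trials in which mediation itself is significant. Counting all trials, with a = 0.5 and a direct effect of 0.25 SD, the rate is about 13% at N = 40 and about 46% at N = 100, because small trials also fail to detect the mediation paths.

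**Weight.** This is the fourth goal and not the primary analysis. The article says it will explore whether mediator changes reduce symptoms, and a bootstrap is already planned. Its statistical section also provides for checking design effects, although the power figures assume independence. All of this is fair and keeps the weight low.

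**Conclusion.** The point holds in limited form. The article attributes to its mediation analyses a property that the design lacks: at N = 100 they cannot establish full mediation without a stated bound, and the direct-effect interval of about ±0.40 to 0.43 residual SD is wide. That figure rests on independent children, a 50 to 50 split and a component-mediator correlation of 0 to about 0.37; clustering by therapy group would widen it. The .80 is arithmetically right but answers a different question.

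The miss rates of about 33 to 38% at 0.5 SD and 78 to 79% at 0.25 SD illustrate what would happen under a non-significance rule and the assumed paths. They are not a property of a rule the article has adopted. The primary analysis is unaffected.

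**What to change.** In the Secondary objectives paragraph of the statistical section:

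1. Replace the partial-or-full determination with a commitment to report, for each component, the indirect effect and the remaining direct effect with bootstrap 95% intervals.
2. State that the power of .80 is for the joint test of component and mediator.
3. Call mediation complete only if the direct-effect interval lies within a margin stated in advance in SD units. Otherwise report that a remaining direct effect cannot be excluded.

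The cost is wording and the choice of a margin; the intervals come from the bootstrap already planned. The downside is that full mediation will rarely be claimable with 100 children.

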## Methods

### Study design

This multi-center study examines the addition of two parental components to a TF-CBT-based treatment for children exposed to IPV, which results in a 2 (preparatory program present versus absent) x 2 (parent-child interaction present versus absent) factorial randomized experimental component trial. The study includes pre-treatment (T1), treatment, post-treatment (T2), and a 6-month follow-up (T3) assessment, and will include 100 children and their custodial parents (Fig. 1 depicts the study design). The baseline assessment (T1, see Fig. 2) will take place one week prior to the start of the 6-week preparatory program. To ensure comparability across treatment conditions, in the “No preparatory program” condition, parents and children will be assessed 7 weeks before the beginning of the TF-CBT-based treatment. Additionally, parents and children will be assessed three times during treatment, namely at the beginning of the intervention (session 1), after sharing the trauma narrative of the child with the parent (session 9), and at the end of the intervention (session 15). These measurements allow us to test mediating pathways [47], and allow us to monitor, and if necessary control for, new IPV or other stressful incidents. The second assessment (T2) will take place one week after the last session of the TF-CBT-based treatment for all four conditions. The third assessment (T3) will be at a follow-up, six months after the last session of the treatment. Regardless of condition, all participants receive the standard TF-CBT-based treatment. The difference lies in the addition of the two parental components. Families who are assigned to “No preparatory program“ or “No parent-child interaction” conditions will not receive an alternative component additionally to standard TF-CBT based treatment.

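### The two mediation models list no baseline mediator or baseline symptom term, so a mediator-symptom association present before treatment can appear as mediation

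*Protocol article*

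**What the plan says.** The statistical section of the protocol article, under Secondary objectives, names two mediation models by their independent variables. One is "A first model with component 1 (preparatory parent program) and parent availability as independent variables". For the other component the article describes, in the same form, "a second model with component 2 (parent-child interaction sessions) and parent-child interaction as independent variables". Power is given for N = 100, alpha .05 and f² = .10: "we will achieve a power of .80 if 2 predictors are tested in the regression". Bootstrapping is planned as a robustness check, and a published set of recommendations is cited for the method.

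Three other statements bear on these models:

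- The opening paragraph of Statistical analyses and sample size calculation covers all analyses and says "we will control for duration and severity of the IPV [45], parental psychopathology [46], and new incidents of IPV".
- The aim is worded as change. The components are expected to raise availability and improve parenting, and then "Also, we will explore whether these changes lead to a reduction in symptoms".
- Baseline data exist: "The study includes pre-treatment (T1), treatment, post-treatment (T2), and a 6-month follow-up (T3) assessment".

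The primary model, by contrast, contains both components and their interaction. Baseline waves of mediators and symptoms are modelled only in the exploratory cross-lagged panel analyses, which are not described as containing the components.

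**The concern.** Randomisation protects the path from component to mediator. It does not protect the path from mediator to symptoms, because parental availability and parent-child interaction are not assigned. The Background itself argues that interparental violence both worsens parenting and raises child symptoms, so the two should already be associated at T1. Several mediator scales and symptom scales are also completed by the same parent, which is a further stable source of correlation.

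A model of post-treatment symptoms on the component and the post-treatment mediator credits that prior association to the mediator. If the component does shift the mediator, as the protocol predicts, the product of the two paths is non-zero even when changing the mediator does nothing to symptoms. Bootstrapping puts an interval around the biased product and does not remove the bias. What is at stake is the mechanism conclusion, which is a named aim of the trial.

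**Working it through.** **1. The plan's own figure.** Noncentral F test with λ = f² × N = .10 × 100 = 10, df = 2 and 100 − 2 − 1 = 97: power .803. The stated .80 is reproduced, so the arithmetic of the power statement is sound.

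**2. Post-treatment scores, no baseline terms.** Assumptions, none given in the documents: unit-variance T1 scores with mediator-symptom correlation −r0, stability s for both, component effect on the mediator 0.5 SD, true mediator effect zero, no contribution from the general covariates.

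Given the component, cov(M2, Y2) = −s²·r0 and var(M2) = s² + (1 − s²) = 1. The two-predictor model therefore estimates b = −s²·r0 instead of 0.

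| r0 | s | b = −s²·r0 | indirect = 0.5 × b | b falsely significant (simulated, N = 100) |
|---|---|---|---|---|
| .3 | .6 | −.108 | −.054 | 19% |
| .3 | .7 | −.147 | −.074 | 30% |
| .4 | .6 | −.144 | −.072 | 29% |
| .4 | .7 | −.196 | −.098 | 51% |

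Hand check of the last row: SE ≈ √((1 − .196²)/97) ≈ .0996, ratio ≈ 1.97, so about half of trials pass the 5% threshold. Both paths are significant together in 13% to 35% of trials. Over a wider range (r0 .2 to .5, s .5 to .7) the rate for b is 8% to 69%.

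**3. Change scores, same two predictors.** Here cov(ΔM, ΔY) = −(1 − s)²·r0 and var(ΔM) = (1 − s)² + (1 − s²) = 2(1 − s), so b = −(1 − s)·r0/2. This runs from −.045 (r0 = .3, s = .7) to −.080 (r0 = .4, s = .6). The false-positive rate for b is about 6% to 12%.

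**4. With the T1 terms added.** In the model of step 2 the rate returns to about 4% to 6%. That follows from the assumption that T1 scores are the whole confounder. A less favourable assumption is a latent stable family factor carrying a share ρ of the variance of each score, so that T1 scores measure it imperfectly. Then b = −ρ without T1 terms and −ρ/(1 + 2ρ) with both.

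| ρ | b without | b with | indirect without | indirect with | both paths significant, without / with |
|---|---|---|---|---|---|
| .3 | −.30 | −.19 | −.15 | −.10 | 60% / 35% |
| .5 | −.50 | −.25 | −.25 | −.13 | 70% / 60% |
| .7 | −.70 | −.29 | −.35 | −.15 | 70% / 80% |

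The estimate shrinks in every row, but at ρ = .7 the rejection rate does not fall, because the standard errors shrink as well.

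**5. When the component does not shift the mediator.** At ρ = .5, b is still biased, but the mean indirect effect is 0.00 and both paths are significant in 4.9% of runs (8.7% with 12 randomised groups of 8 and an assumed intraclass correlation of .10).

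**6. The other component.** In a balanced 2 × 2 it is orthogonal to the first. If it moves mediator and symptoms by 0.5 SD each, with no family factor, omitting it gives b = −(.5 × .5 × .25)/(1 + .25 × .25) = −.0625/1.0625 ≈ −.06, and an indirect effect of about −.03.

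**7. Power after the change.** Testing the same two terms with five predictors in the model (df 2 and 94, λ = 10) gives .802. With three further control covariates it is again .802. Only an omnibus test of all five predictors at the same f² would lose power (.648), and that test is not needed.

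**The case against.** A reader might infer that the models contain two predictors and nothing else. The text does not support that. The two-predictor sentence is a power statement about tested terms, and the general paragraph adds covariates that describe family circumstances and may absorb part of the confounding. The simulations in step 2 give those covariates no role. This objection stands, but none of them is the T1 mediator or T1 symptoms.

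The aim is worded as change, which leaves room for change scores, and under that reading the inflation is modest. This also stands, and it makes the size conditional. The listed variables do not say which reading applies.

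The cross-lagged analyses do model T1 levels and stability. They are labelled exploratory and are not described as containing the components, so they do not replace the mediation test. The cited recommendations cannot be checked from the article, and a general citation does not change the variables the text lists.

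Finally, this is a secondary analysis, and the link from changed parenting to symptoms is one the authors say they will explore. That limits the importance of the point but leaves the bias in place.

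**Conclusion.** The point holds in a conditional form. As listed, the mediation models have no T1 mediator or T1 symptom term. If post-treatment scores are entered, a prior mediator-symptom association can pass for mediation whenever the component shifts the mediator. Under the assumed correlations (.3 to .4), stability (.6 to .7) and a 0.5 SD shift, the mediator path is falsely significant in about 19% to 51% of trials, or about 6% to 12% with change scores. These inputs are assumptions.

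Three stronger conclusions are not supported:

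- That baseline adjustment restores a 5% error rate. This is true only if T1 scores capture the whole confounder. With an imperfectly measured family factor at ρ = .5 the bias is halved, not removed.
- That leaving out the other component lets stable family differences in. It is a randomised, orthogonal factor, and its omission has a small effect.
- That the trial's efficacy result is compromised. The primary analysis does not use these models.

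**What to change.** Write out the two equations for each mediation model:

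- **Mediator:** on both component indicators and the T1 mediator.
- **Symptoms:** on both component indicators, the mediator, the T1 mediator and T1 symptoms.

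Keep the general covariates already planned. Use the T1 mediator where it was measured at T1. The parent-child concordance measure (sessions 1, 9 and 15) and the session 6 comparison have no T1 value and should be identified as such. Bootstrap the indirect effect from these equations. State that the two predictors in the power sentence are the tested terms, with the others as covariates. Say that the mediator-symptom path is non-randomised evidence and may retain confounding after adjustment. Including the other component is mainly for consistency with the 2 × 2 design.

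The cost is three more terms from data already in the plan and a few degrees of freedom. Power for the two tested terms goes from .803 to .802.
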